**18 Appendix 1 Study ammendments after 1/3/10**

# Study Summary

**Title**

The effect of Vitamin D on the microcirculation of patients with chronic kidney disease (CKD) and vitamin D deficiency

**Protocol Version Number and Date**

Version 1.3, 25/2/10

**Short Title**

Vitamin D, CKD and the microcirculation

**Methodology**

Double blind, randomised controlled trial comparing oral ergocalciferol with placebo in patients with chronic kidney disease and vitamin D deficiency.

**Study Duration**

Each patient studied for 7 months. We anticipate 6 months to complete recruitment. Post study analysis will take approximately 4 months.

See appendix 1 for additional study details

**Study Centres**

The Royal London Hospital, London, UK

**Objectives**

To determine if vitamin D therapy in a cohort of patients with chronic kidney disease and vitamin D deficiency improves microcirculatory function, progression of chronic kidney disease and other key cardiovascular parameters.

**Number of Subjects/Patients**

80 patients (40 in each arm)

15 normal, healthy subjects will also be recruited to determine normal values for the study procedures

**Main Inclusion Criteria**

Inclusion criteria: eGFR between 15 and 60 ml/min/1.73m^2^, vitamin D levels <40nmol/L, no evidence of diabetes mellitus and not receiving either haemodialysis or peritoneal dialysis. Age 18-80

**Statistical Methodology and Analysis**

All data will be analysed by the principal investigator with the support of a trained statistician and the chief investigator. The data will be assessed for normality and the relevant parametric or non−parametric tests applied. The statistical programmes SPSS and STATA will be used.

# Glossary of abbreviations – study specific

| **ADMA - asymmetric dymethyl arginine**  Naturally occurring inhibitor of nitric oxide. Causes vasoconstriction, hypertension and  impaired endothelium dependent vasodilatation. |
| --- |
| **Cardiac MRI – Magnetic resonance imaging**  Detailed imaging of the heart and its surrounding structures. This technique uses no radiation, rather magnetic fields and radio waves generate highly detailed anatomical images |
| **CKD – chronic kidney disease**  A state of chronically impaired kidney function leading to a major increase in cardiovascular morbidity and mortality. It is a global health problem with an increasing incidence and prevalence. |
|  |
| **ECG - elctrocardiogram**  A non-invasive test used to measure heart rate, rhythm and some morphological features  **Echo – echocardiogram**  A non-invasive ultrasound assessment of the structure and function of the hear and surrounding structures |
| **eGFR – estimated Glomerular filtration rate**  A value generated by validated estimation equations which converts serum creatinine into a more functional assessment of kidney function. Expressed as ml/min/1.73m^2^ and usually referred to as a percentage of kidney function. |
| **eNOS – endothelial nitric oxide synthase**  An endothelial based enzyme which converts L-arginine to nitric oxide |
| **ESRD – end stage renal disease**  Occurs when there is a very low glomerular filtration rate. Usually associated with significant symptoms and usually requires intervention with renal replacement therapy such as dialysis or transplantation |
| **Iontophoresis**  A non-invasive test to determine microvascular function in the skin. A very small electric current delivers vasoactive drugs to the dermis and response in the blood vessels is measured by a laser Doppler probe. |
| **Laser Doppler flowmetry**  The non-invasive measurement of red blood cell flux in skin micro-vessels by using laser Doppler probes. |
| **LV mass – left ventricular mass**  Measured mass in grams of the left ventricle. Elevated values are associated with disease states such as hypertension. This can readily be assessed by cardiac MRI |
| **Oxidative stress**  A state of adverse chemistry at a cellular level which can lead to cell dysfunction and death. Mediated by reactive oxygen species |
| **PCR – protein/creatinine ratio**  A measure of protein in the urine reflecting Glomerular injury. More sensitive than urine dipsticks. |
| **PWV – pulse wave velocity**  A non-invasive measure of vascular health. Blood pressure cuffs around the neck and thigh inflate and deflate to measure the speed of single pulse waves. Higher values are found in disease states. |
|  |
| **Skin AF -Skin autofluorescence**  A non-invasive measure of accumulated metabolic end products which correlate to overall vascular health.  **SDF – side stream dark field imaging**  This imaging technique utilizes a novel method of reflectance avoidance in which the illuminated light and reflected light travel via independent pathways. Sub lingual capillaries can be imaged in this way. An analysis of the moving cells in the images permits the quantitative measurement of red blood cell flow in the capillaries.  **Glossary of terms – study non-specific**  **AE** Adverse Event  **AR**  Adverse Reaction  **ASR**  Annual Safety Report  **CI** Chief Investigator  **CRF**  Case Report Form  **JRO**  Joint Research and Development Office  **IMP**  Investigational medicinal product  **NHS R&D** National Health Service Research & Development  **PI** Principle Investigator  **QA**  Quality Assurance  **QC** Quality Control  **RCT** Randomised Control Trial  **REC**  Research Ethics Committee  **SAR** Serious Adverse Reaction  **SAE** Serious Adverse Event  **SOP**  Standard Operating Procedures  **SmPC**  Summary of Product Characteristics  **SSAR** Suspected Serious Adverse Reaction  **Subject**  An individual who takes part in a clinical trial  **SUSAR** Suspected Unexpected Serious Adverse Reaction |
|  |

# Introduction

## Background

Cardiovascular (CVS) diseases are the major cause of death in patients with renal failure, accounting for approximately half of all deaths (1). Patients with CKD are far more likely to die of cardiovascular disease than progress to end stage renal disease (ESRD) (2). Recently, vitamin D deficiency has been identified as a non-traditional CVS risk factor (3,4,5). Currently, vitamin D is not routinely prescribed in the early stages of CKD.

Vitamin D has been shown to improve microcirculatory function in diabetic patients with vitamin D deficiency (6). Microcirculatory dysfunction itself is now considered a marker of cardiovascular health and a predictor of future cardiovascular events (7)

A number of recently published observational studies (8,9,10) provide support to the possible CVS protective role of vitamin D in the ESRD population. These studies describe the effect of vitamin D analogues on all-cause and CVS mortality in patients on haemodialysis, and demonstrated that mortality was inversely related to treatment with vitamin D analogues.

There is a pressing need to examine the effects of vitamin D therapy in the early stages of CKD. Early detection of microcirculatory dysfunction, before ESRD is reached, will provide a powerful tool for predicting future CVS events and thus provide an opportunity to intervene with therapies including vitamin D at an early stage of renal dysfunction. This will determine if important reductions in CVS risk can be achieved at a stage when the vascular system is likely to be more responsive to pharmacological intervention and where the risk of CVS events far outweighs the progression to ESRD.

This trial will establish both the therapeutic benefit of early treatment with vitamin D and determine how the microcirculation responds to vitamin D therapy at a clinical and in vitro level. Potential benefits include the long term reduction of CVS risk by determining the place of vitamin D therapy in early CKD, establishing how microcirculatory assessments can be utilised in clinical practice and further studying the link between endothelial dysfunction and vitamin D deficiency.

## Investigational Agent

Ergocalciferol - Vitamin D2, a fat-soluble vitamin important for many biochemical processes including the absorption and metabolism of calcium and phosphorus. In vivo, ergocalciferol is formed after sun (ultraviolet) irradiation of plant-derived ergosterol, another form of vitamin D occurring naturally in human skin.

Ergocalciferol is used to treat chronic hypocalcemia, hypophosphatemia, rickets, and osteodystrophy associated with various medical conditions including chronic renal failure, familial hypophosphatemia, and hypoparathyroidism (postsurgical or idiopathic, or pseudohypoparathyroidism).

Ergocalciferol is indicated for the prevention and treatment of vitamin D deficiency states. Vitamin D deficiency may occur as a result of inadequate nutrition, intestinal malabsorption, or lack of exposure to sunlight, but does not occur in healthy individuals receiving an adequate balanced diet and exposure to sunlight.

Vitamin D is essential for promoting absorption and utilization of calcium and phosphate from the intestine and for normal calcification of bone. Along with parathyroid hormone and calcitonin, it regulates serum calcium concentrations by increasing serum calcium and phosphate concentrations as needed. Vitamin D stimulates calcium and phosphate absorption from the small intestine and mobilizes calcium from bone.

The molecular weight of ergocalciferol is 396.65. It has a plasma half life of 19 to 48 hours (stored in fat deposits in body for prolonged periods).

A dose of 1.25mg (50,000IU) to 5mg daily has been recommended. The dose should be adjusted according to the severity of the condition. This medicine is delivered by oral administration

Adverse events are generally associated with excessive intake of ergocalciferol leading to the development of hypercalcaemia. The symptoms of hypercalcaemia can include; anorexia, nausea, vomiting, diarrhoea, loss of weight, headache, polyuria, thirst, vertigo, constipation, fatigue, bone pain, muscle weakness, abdominal pain, mental disturbances, impaired renal function, kidney stones and cardiac arrhythmias.

A single acute overdose is virtually non-toxic and requires supportive treatment with liberal fluids only. Treatment of chronic overdose with resulting hypercalcaemia consists of immediate withdrawal of the vitamin, a low calcium diet, and generous fluid intake. Severe cases may require hydration with intravenous saline together with symptomatic and supportive treatment as indicated by the patient's clinical condition. Plasma calcium and U&E's should be monitored.

## Preclinical Data

The endothelium is strategically located between the muscular wall of blood vessels (of all sizes) and the blood stream. It responds to stimuli including pressure, shear stress, and hormonal agents which mediate relaxation and contraction of the underlying vascular muscular wall. These stimuli prompt endothelial cells to release agents that regulate vasomotor function, trigger local inflammatory reactions, and affect homeostasis (11).

Endothelial dysfunction results in reduced vasodilation, a pro-inflammatory state, and pro-thrombotic consequences that predispose to artherosclerotic plaque formation which in turn is associated with cardiovascular disease processes, including hypertension (12), coronary artery disease (13), chronic heart failure (14), peripheral artery disease (15) and diabetes (15).

Reduced endothelial vasodilatory responses are mainly caused by reduced nitric oxide generation due to down-regulation of eNOS, the enzyme mostly responsible for its generation. This process has been shown to be multi-factorial (16,17,18,19).

Recent unpublished evidence also suggests that vitamin D deficiency can impair the activation of eNOS. A study involving vitamin D receptor knock out mice, where eNOS activity was reduced, showed reversal of endothelial dysfunction by calcium supplementation (20). It has also been shown that exogenous vitamin D prevents platelet activation and platelet-monocyte aggregate formation due to down regulation of the renin-angiotensin system (21,22). It is thought that these processes will accelerate atherosclerotic plaque formation.

However, many important markers of endothelial health and function have not been assessed in the setting of a clinical trial. This study will provide an opportunity to study the endothelium at a cellular level to determine the molecular pathways by which vitamin D therapy mediates its effects.

**1.4 Clinical Data to Date**

It is logical to study the earlier stages of CKD to determine if therapeutic interventions can reduce cardiovascular morbidity and mortality. However, current data regarding vitamin D and CKD is observational (23) and a large, prospective, randomised controlled trial of vitamin D therapy in CKD patients, with particular focus on the microcirculation, has yet to be conducted (24). The status of the microvascular beds of both the heart and kidney are reflected by subdermal capillary function (25,26). However, intricate analysis of the effects on the microcirculation of vitamin D supplementation in a population with CKD has yet to be undertaken. A recent review article (27) has highlighted the need for further assessments of microcirculatory dysfunction in patients with CKD as a method for predicting adverse CVS outcomes.

## 1.5 Dose Rationale and Risk/Benefits

A dose regimen of ergocalciferol 50,000 IU weekly for 12 weeks and then monthly for 3 months has been shown to be effective at both raising serum vitamin D levels and lowering PTH levels in a similar cohort which is the precise effect we hope to achieve in our study group (28). No patient developed the most common side effect of hypercalcaemia and no other adverse effects were reported. A further study (29) of weekly ergocalciferol (50,000 IU/week for 24 weeks) was also shown to raise serum vitamin D levels with no adverse events reported. We have chosen the dose regimen in the K/DOQI guidelines for the replacement of vitamin D in patients with CKD. This consists of 50,000IU of ergocalciferol weekly for 1 month and then monthly for 5 months. As in the studies above, we anticipate a rise in serum vitamin D levels to therapeutic but well below toxic levels.

## 1.6 Rationale and Risk/Benefits

Techniques to assess the microcirculation are quick, non-invasive and reproducible and could become a powerful risk assessment tool available in routine clinical practice. A number of studies assessing vitamin D therapy in CKD are underway (30), but none have undertaken an analysis of microcirculatory dysfunction either in vivo with clinical assessments of microcirculatory function or in vitro by determining the mechanism of action of vitamin D on the endothelium.

This trial offers a unique opportunity to evaluate the place of vitamin D therapy in early CKD. By furthering our knowledge of the in vitro and in vivo effects of vitamin D therapy in patients with CKD, we will have the opportunity to enhance current practice, further reduce CVS risk and develop a greater understanding of the interaction between vitamin D and the endothelium.

# Study Aims and Objectives

**Primary study objective** – to evaluate the effects of vitamin D on the microcirculation of patients with chronic kidney disease (CKD) and vitamin D deficiency.

**Secondary study objective** – to evaluate the effects of vitamin D on key clinical parameters in patients with chronic kidney disease (CKD) and vitamin D deficiency.

# Study Design

## General Design

Single centre, double blind, randomized control trial of oral ergocalciferol compared to placebo.

## Primary Study Endpoints

**1. Microcirculatory studies** – pulse wave velocity (PWV), iontophoresis of acetyl choline (AcH) and sodium nitroprusside (SNip), skin autofluoresence (AF) and side stream dark field imaging of the sub lingual microcirculation.

Pulse wave velocity – we expect PWV to decrease after vitamin D therapy.

Iontophoresis – we expect lower skin micro-vessel resistance as measured by laser Doppler Flowmetry (LDF) after vitamin D therapy.

Skin autofluorescence – we expect lower deposition of advanced glycation end products after vitamin D therapy.

Sublingual microvascular flow using sidestream darkfield (SDF) imaging – we expect enhanced flow in patients treated with vitamin D

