## Prior and Concomitant Therapies

Prior therapies:

There will be a washout period of 2 weeks for all vitamin D therapies currently being taken by participants. The most commonly prescribed oral vitamin D analogues all have a half life of less than 14 days (Alfacalcidol— 3 hours, Calcitriol—3 to 6 hours, Ergocalciferol—19 to 48 hours) (34). Participants will be screened for use of all over the counter medicines which may contain vitamin D. It is very unlikely patients will suffer any side effects from stopping these medications for this period. Patients will be reassured about the safety of drug withdrawal and the safety and validity of undertaking a randomized, placebo controlled trial. Given that routine supplementation with vitamin D in early CKD is not routine, we anticipate that very few individuals will actually need to stop vitamin D analogues.

The patient’s general practitioner will be contacted to ensure no medicines that may contain vitamin D are being taken by participants without their prior knowledge and that no depot vitamin D preparations have been dispensed in the last 6 months.

Concomitant therapies:

Blood pressure medication should be unchanged for study period but additional therapies can be added at the discretion of the investigators if blood pressure requires clinical intervention on safety grounds. General practitioners will be asked to maintain BP medications at a stable dose. Any changes in medication by the study team will be communicated to GP’s in writing and included in the CRF. Patients will be asked to take any concomitant therapies which can affect microvascular function after clinic visits at which these assessments are made (visits 2,3,4,6,9)

Drugs which are likely to have these particular effects include aspirin and vasodilating anti-hypertensives such as calcium channel blockers. There is no evidence to suggest that iontophoresis of acetylcholine (Ach) and sodium nitroprusside (SNip) is directly affected by the presence of any antihypertensive drugs. However, there is a theoretical chance that there may be some affect on vasodilatiation particularly by drugs with a known vasodilatory effect eg calcium channel blockers. Hence, patients will be asked to take all their daily medications after all microcirculatory assessments have been made.

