1. Pulse wave velocity. An assessment of the speed of the pulse transmission in the major blood vessels of the body. Patients will have blood pressure cuffs placed around the thigh and neck. The cuff around the neck poses NO DANGER TO THE PATIENT AS IT ONLY INFLATES TO 60mm Hg – BELOW SYSTOLIC BLOOD PRESSURE. At worst, patients may feel a gentle pressure sensation around the neck. FULL RESUCITATION EQUIPMENT IS AVAILABLE ON SITE AND THE INVESTIGATORS AND CLINIC STAFF ARE TRAINED IN ADVANCED LIFE SUPPORT TECHNIQUES

Duration – 5 minutes

2. Iontophoresis. An assessment of skin microvascular function. Two compounds (AcH and SNip) are transmitted through the skin by the use of a very low electrical current into the small blood vessels located just under the skin. A laser Doppler probe records the response of the microvasculature. This is a non-invasive test and the drug dose is too low to cause any systemic absorption. Minor skin irritation has been reported but is usually mild and self limiting.

Duration - 15 minutes

3. Skin autofluorescence – An assessment of the build up of advanced glycation end products (AGE), which are a marker of oxidative stress. Patients place their arm over an ultraviolet light and results of AGE product accumulation are downloaded to a computer. This is a painless and non-invasive test.

Duration – 5 minutes.

Sublingual microvascular flow using sidestream darkfield (SDF) imaging – this is a non-invasive imaging tool to assess intra-vital capillary blood flow. A small camera (0.7cm) with a replaceable sterile cap is placed under the tongue in a similar way to temperature measurement with a mercury thermometer. 3 separate images are collected during one reading. These recordings will occur at visit 3, 6 and 9.

Duration – 5 minutes

**SF 36 –** Patients will be asked to fill in this standardized questionnaire about quality of life.

Duration - 10 minutes.

**Urine –** patients will be asked to give a clean catch urine specimen when they arrive at clinic which will be divided into 3 samples (urine sodium, urine calcium and urine PCR). Urine samples will be spun down so no cellular component will be retained or studied.

Duration – 5 minutes

**MRI –** Cardiac MRI scanning will take place at the London Chest Hospital and will be supervised by specialist medical and radiography staff. We will measure left ventricular mass and ejection fraction. The examination will not usually require contrast media to be injected.

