# 7. Statistical Plan

## Sample Size Determination

This study is powered to detect a difference in microcirculatory function as assessed by iontophoresis. It is likely that if a difference is seen in microcirculatory function as assessed by iontophoresis that the other microcirculatory assessments will follow the same trend

We expect 85% failure in the placebo group and 50% failure in the intervention arm (35% difference in success). We have set alpha=0.05 and beta=0.1 which gives us 90% power.

Therefore:

n=[((15x85)+(50x50))/35^2]x10.5=32 patients in each arm

In order to ensure we achieve a total of 32 patients in each arm for an adequately powered study, we will recruit 40 patients per arm to allow for withdrawals and protocol violations.

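### The plan does not secure a 5% overall error for its primary conclusion: five unranked primary measurements, sizing on iontophoresis alone, and no primary agonist, visit, success rule or adjustment

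*Combined protocol and SAP*

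**What the plan says.** Primary Study Endpoints places four techniques under one heading: "pulse wave velocity (PWV), iontophoresis of acetyl choline (AcH) and sodium nitroprusside (SNip), skin autofluoresence (AF) and side stream dark field imaging". With two agonists for iontophoresis this makes five measurements. The section gives an expected direction for each technique but no order of importance.

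Sample Size Determination treats iontophoresis differently: "This study is powered to detect a difference in microcirculatory function as assessed by iontophoresis". It expects that, if iontophoresis shows a difference, "the other microcirculatory assessments will follow the same trend". The error rates appear once, in that calculation: "We have set alpha=0.05 and beta=0.1 which gives us 90% power". The outcome there is binary, with 85% failure on placebo against 50% on active treatment. Failure is not defined, and neither agonist nor visit is named.

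Statistical Methods says that differences between means will be compared by Student's t test, with multiple regression to look for associated factors. The Study Summary adds that the choice between parametric and non-parametric tests follows a check of normality. Neither gives a primary time point, a significance level per test, a success rule (any or all) or an adjustment.

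Microcirculatory assessments fall at visits 2, 3, 4, 6 and 9 (Prior and Concomitant Therapies), and randomisation is at visit 3. Sublingual imaging is at visits 3, 6 and 9 only. The additional arm in Appendix 1 ends at visit 6 and keeps the microcirculatory assessments unchanged.

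**The concern.** A primary conclusion needs a rule, fixed in advance, that says which result counts. Here a reader of the final report could not tell whether success meant the acetylcholine response, the nitroprusside response, any one of five measurements, or all of them. The stated alpha and power belong to one comparison that is only partly identified.

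Both rules that the silence allows undo part of what the plan states. Under an any-one rule without adjustment, the chance of a false primary finding exceeds 5%. Under an all-must-succeed rule, the error is controlled, but power falls below the 90% calculated for a single comparison. What is at stake is whether a nominally significant primary result from this trial can be taken at its stated error rate.

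**Working it through.** **Inputs.** Five primary measurements (Primary Study Endpoints). Alpha 0.05, power 90%, failure 85% against 50%, 32 per arm analysed and 40 recruited (Sample Size Determination). Correlations between measurements are not in the documents, so a range of 0.3 to 0.8 is assumed.

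**1. The plan's own figure.** The plan gives "n=[((15x85)+(50x50))/35^2]x10.5=32 patients in each arm".
- (1275 + 2500)/1225 × 10.5 = 3.0816 × 10.5 = 32.36. The plan's 32 is reproduced.
- The factor 10.5 is (1.960 + 1.282)², so the calculation is for one two-sided test at 0.05.
- The sample size is therefore not wrong for a single comparison.

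**2. If any one of the five at the final visit could count as success, each at two-sided 0.05.**
- Independent tests: 1 − 0.95⁵ = 1 − 0.7738 = 22.6%.
- Correlated tests (equicorrelated normal test statistics, 200,000 simulated draws):

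| Assumed correlation | Family-wise error |
|---|---|
| 0.3 | 20.8% |
| 0.5 | 18.2% |
| 0.8 | 12.8% |

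**3. If only iontophoresis counted, but either agonist could succeed at the final visit.** Independent tests: 1 − 0.95² = 9.75%. At a correlation of 0.8 it is 7.8%. Naming the technique without the agonist is therefore not enough.

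**4. If all five had to succeed.** Error does not exceed 5%. Joint power cannot exceed that of the weakest measurement, and only iontophoresis has a power calculation. As an illustration, five independent tests each with 90% power succeed together with probability 0.9⁵ = 59%.

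**5. Cost of keeping five alternatives with Bonferroni.** The level per test is 0.05/5 = 0.01.
- The plan's formula becomes 3.0816 × (2.576 + 1.282)² = 45.9, so 46 per arm. With the same 20% allowance, 46/0.8 = 57.5, so 58 recruited per arm.
- With 32 per arm, power is Φ(0.35/√(0.3775/32) − 2.576) = Φ(0.647) = 74%, where 0.3775 = 0.85 × 0.15 + 0.50 × 0.50.

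**The case against.** The strongest reply is that the plan does give iontophoresis a lead role: the trial is sized on it, and the other assessments are expected to follow it. On that reading the remaining measurements are supportive and 0.05 applies to one test. This has some force, and it is why iontophoresis is the natural choice in the fix. But an expected trend is not a testing rule, and iontophoresis itself still has two agonists, several visits and no stated summary.

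A second reply concerns what the documents actually say. A reader might infer that each measurement is tested at 0.05 and that any one significant result is a win, so that the 5% level is definitely breached. No section says either. Alpha appears once, and co-primary in its strict sense would mean that all must succeed. The supportable statement is that control is not secured.

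Three further inferences do not stand:
- **Fourteen primary tests.** Four measurements at visits 4, 6 and 9, plus sublingual imaging at 6 and 9, make 4 × 3 + 2 = 14, and 1 − 0.95¹⁴ = 51%. But the schedule lists measurements, not confirmatory tests at each visit.
- **Sides and current steps.** The operating procedures describe how readings are obtained. They do not present left and right sides or current steps as separate tests.
- **Pulse wave velocity and skin autofluorescence do not count.** The plan describes the former as "An assessment of the speed of the pulse transmission in the major blood vessels of the body", which sits uneasily under a microcirculatory heading. Whether these two measure the microcirculation is a question of construct, separate from error control.

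Finally, the two-sided figures count significant harm as well as benefit. In the favourable direction only, five independent tests give 1 − 0.975⁵ = 11.9%, against 2.5% for one test. The inflation remains, but 22.6% is not the chance of a false claim of benefit.

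**Conclusion.** The point holds as a gap in the plan, not as a demonstrated breach. Five unranked primary measurements, one alpha attached to iontophoresis, and no primary agonist, visit, success rule or adjustment mean that 5% overall error and 90% power are not jointly secured for the primary conclusion.

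The size depends on a rule that the plan does not state. For five measurements at the final visit with any one sufficient, two-sided error is 22.6% under independence and about 13% to 21% at assumed correlations of 0.8 to 0.3. With all five required, error holds and power is lost. The correlations are assumptions, and a common value for every pair is a simplification. The calculation of 32 per arm stands for one binary comparison under the plan's own formula.

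**What to change.** Before unblinding, amend the plan as follows.

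1. Name iontophoresis as the single primary endpoint, with one agonist, one summary of the response and one visit. Acetylcholine is consistent with the endothelial rationale in Preclinical Data. The visit would be visit 9 in the main trial and visit 6 in the Appendix 1 arm, which has no visit 9.
2. Make the other agonist, pulse wave velocity, skin autofluorescence, sublingual imaging and the earlier visits secondary, tested in a fixed order or with Holm.
3. Align the primary with the sample size. Either define the binary failure and analyse it as a proportion, or state that 32 per arm was calculated for a binary outcome and does not establish 90% power for a continuous summary compared by t test. The documents give no mean difference or standard deviation from which to calculate that power.

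The cost is protocol and SAP wording; no measurement changes. With the binary option, the plan's 32 analysed and 40 recruited per arm can stand. With a continuous summary, the power is unknown until it is calculated. The sponsor can no longer claim primary success on pulse wave velocity, autofluorescence, sublingual imaging or the other agonist alone.
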